## 3. Methods/Design

### 3.1. Study design and setting

This pilot randomized controlled trial (RCT) (NCT05818189) uses a parallel, double-blinded (investigators and participants), single-center design, to compare the effects of personalized tactile cueing versus fixed tactile cueing. The participants will not know which intervention is favored for improving gait automaticity, and the researchers collecting and analyzing the data will not know which intervention group participants were randomly assigned. Only the study coordinator and the laboratory engineer will know the intervention after the randomization to coordinate the visits and home intervention (see Figs 1 and 2). The allocation ratio will be 1:1, and the unit of randomization will be each participant.

**Fig 1 pone.0336859.g001:**
[figure not shown]
CONSORT flow diagram.

**Fig 2 pone.0336859.g002:**
[figure not shown]
Activities and assessments during the clinical trial. See the section “Clinical and cognitive assessments” for the specific list of scales used.

A two-phase screening procedure will be conducted to determine participant eligibility. During Laboratory Visit 0, researchers will administer a clinical assessment and brief questionnaires in person to confirm inclusion criteria. Eligible participants will then be randomized via the REDCap randomization module, programmed by a blinded biostatistician, and assigned to either the personalized or fixed tactile cueing group.

At Laboratory Visit 1, a separate blinded researcher will conduct the baseline mobility assessment, which includes walking and turning trials using fNIRS and three wearable sensors (placed on the feet and lumbar region), as well as additional clinical and cognitive tests. Following this, the blinded researcher will leave the room and an unblinded coordinator and engineer will enter the lab to explain and configure the assigned cueing modality (approximately 15 minutes). The blinded researcher will then return to administer the same mobility protocol with cueing in place.

After completion of the laboratory assessment, a research team member will instruct the participants how to use, wear, and charge the cueing system (either fixed or personalized) and the wearable sensors for mobility monitoring and cueing at home. Participants will wear two instrumented socks and a lumbar sensor continuously for two weeks. They will be instructed to use the cueing system only during the second week of home monitoring.

To promote participant retention through all the study components, we will maintain regular contact with participants through a dedicated study coordinator who will be available to address any questions or concerns. We will also provide flexible scheduling for the visits and send appointment reminders via text or email. To compensate for their time and effort, participants will receive a monetary incentive at the completion of each visit and after each week of home participation.

Screening, intervention, and assessment visits will take place at the Balance Disorders Laboratory at Oregon Health & Science University (OHSU) in Portland, Oregon, USA. Daily life gait monitoring and cueing use will occur in participants’ homes.

### 3.2. Recruitment, screening and consent

Recruitment will be conducted via an existing database of people with PD, who have given informed consent to save and use their contact information for study participation, by referral of movement disorders specialists in the Portland metro area, and through community outreach events. Potential participants will be informed about study procedures and goals. If interested, inclusion and exclusion criteria will be evaluated by phone screening and Laboratory Visit 0. For people who wish to participate, an informed consent will be presented and explained verbally to the participants. The informed consent includes details on the purpose of the study, what the participants will do, possible risks and benefits of the study (without assigning superiority to any intervention). The consent also informs the participants that they may withdraw from the study at any time without penalty. Participants will be given ample opportunity to read, ask questions, and when satisfied, document their consent to participate by signing the informed consent form (written).

The start and end of the recruitment period are 1/15/2025 and 10/01/27 respectively.

*Inclusion criteria:* People with idiopathic PD, age range 55–85 years old, without musculoskeletal or peripheral or central nervous system disorders (other than PD) that could significantly affect their balance and gait. All participants will be capable of following directions for the protocols and giving informed consent. The UK Brain Bank criteria will be used for idiopathic PD diagnosis; i.e., bradykinesia and at least one of the following: rest tremor (4–6 Hz), muscular rigidity, and postural instability not caused by visual, vestibular, cerebellar, or proprioceptive dysfunction. Three or more of the following must be present for the diagnosis of idiopathic PD: unilateral onset, rest tremor, progressive, persistent asymmetry, and responsiveness to levodopa [49]. All PD participants will be Hoehn & Yahr Levels II-III.

*Exclusion criteria:* 1) Parkinson plus syndromes such as progressive supranuclear palsy, multiple system atrophy, corticobasal syndrome, possible vascular parkinsonism, 2) implanted electrodes for deep brain stimulation (DBS), 3) current use of dopamine-blocking agents or cholinesterase inhibitor (as may affect PFC activity while walking), 4) severe dyskinesia that may affect the quality of fNIRS, 5) major musculoskeletal or neurological disorders, structural brain disease, epilepsy, acute illness or health history, other than PD, significantly affecting gait and turning, i.e., peripheral neuropathy with proprioceptive deficits, musculoskeletal disorders, vestibular problem, head injury, stroke, 6) MoCA < 21 or dementia that precludes consent to participate or ability to follow testing procedures [50] and 7) Inability to stand or walk for 2 minutes without an assistive device.

Full ethical approval has been granted by the Oregon Health & Science university IRB (24837), in accordance with the principles of the Declaration of Helsinki.

### 3.3. Randomization and blinding

At the end of Laboratory Visit 0, participants will be randomized into either the personalized or fixed tactile cueing based on computer generated blocks with randomly permuted block size (2–6). We will use a stratified randomization to balance the disease severity per group, using Hoehn and Yahr (2 or 3) and FoG status (yes or no) (New Freezing of Gait Questionnaire (NFOGQ) Q1) [51]. Randomization procedures are fully concealed, and group allocation is conducted automatically within REDCap (a blinded statistician generated the stratification matrix). The information is only known by the study coordinator and the engineer, who are not participating in the data collection and data analysis. Different levels of access to REDCap are set for the study staff to prevent unblinding.

### 3.4. Assessment procedures

#### 3.4.1. General procedures.

Fig 2 below illustrates the flow of study activities. After screening and randomization, the immediate effect of the cueing interventions will be assessed during a study visit to the laboratory (Visit 1) through measures of cortical activity and functional mobility. Additionally, clinical and cognitive scales will also be conducted during this visit.

The main outcomes will be measured in the ON-medication state (after approximately 1-hour from last intake) before and while using their assigned tactile cueing mode (personalized or fixed). During the assessment, participants will complete the following mobility tasks, first without cueing and then with cueing activated: 1) 2-minute walking, 2) 2-minute walking with a concurrent cognitive dual-task, 3) 1-minute 360 degrees turning in place, and 4) 1-minute 360 degrees turning in place with a concurrent cognitive dual-task.

The gait task consists of two minutes of walking back and forth along a 9-meter hallway at comfortable speed. The turning task involves alternating 360° turns (right and left) in place for one minute. The secondary cognitive task used in both dual-task conditions is a modified version of the Continuous Performance Test–AX (AX-CPT), which assesses attention and vigilance.

Throughout the mobility protocol, participants will wear a portable fNIRS system (Brite and OctaMon, Artinis) and three wireless inertial sensors (APDM Precision Motion, Clario) positioned on the posterior trunk and both feet to objectively measure cortical activity while performing gait and turning tasks.

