Behaviorally, increased variability in gait (stride time, stride length, gait speed variability) [8,21] and impaired turning (velocity, smoothness) [22,23] have been associated with reduced automaticity. In healthy older adults, such variability remains stable during dual-task walking, whereas in PD, variability increases, suggesting increased reliance on cognitive control [24,25]. Turning appears particularly sensitive to automaticity loss [22]. However, gait and turning variability can also be influenced by freezing of gait (FOG) and postural instability, complicating interpretation [21,26]. Therefore, increased variability during gait and turning may not necessarily represent an automaticity decrement, so measuring cortical activity directly while walking would help validate automaticity changes [10]. Additionally, other studies show that very low and very high gait variability (U-shaped trend) could be associated with subclinical basal ganglia damage [27]. Thus, combining cortical and behavioral measures together may offer a more complete understanding of gait automaticity in PD, critical to developing improved rehabilitation strategies.

Current treatments for PD, such as levodopa or deep brain stimulation, do not reliably improve automaticity in PD. Levodopa does not improve, and may worsen, balance and attention [28,29], while deep brain stimulation offers limited benefits for balance or cognitive function [30]. As a result, alternative and complimentary interventions are needed.

Cueing, using external temporal or spatial stimuli like auditory, visual, or tactile stimuli [31], can improve gait, turning, and FOG [32]. Its effects vary depending on the cueing modality, medication state, and individual impairments [32]. However, the neural mechanisms underlying cueing remain unclear, particularly its impact on cortical areas like the PFC [33–36]. If cueing with external stimuli while walking requires increased cortical attention, we will see increased PFC activity, whereas if cueing improves automaticity, we will see decreased PFC activity. Thus, it is necessary to better understand the impact of different cueing modalities on the cortical and behavioral correlates of automaticity, to improve the effectiveness of cueing [37].

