## 2. Objectives

The primary objective of this trial is to assess immediate changes in cortical activity during walking with two types of tactile cueing in people with PD, and whether these changes are accompanied by improvement in gait and turning (laboratory testing). We hypothesize that personalized tactile cueing will reduce PFC activity (improve automaticity) and reduce gait variability (as well as improve gait and turning speed). We also expect to observe increased activity in the primary sensory cortex with this type of personalized cueing that may require sensorimotor planning. In contrast, we predict that the fixed cueing will increase PFC activity and increase gait variability (need for more attention to the cues). An exploratory objective is to evaluate the feasibility and potential benefits of using tactile cueing during daily life.

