### 3.4. Outcome measures

Primary and secondary outcome measures are summarized in Table 1, which includes the domains and metrics. These measures have been selected based on 1) potential relation to gait automaticity (PFC activity and gait variability) and 2) response to cueing (stride time, LDS, turn duration, turn jerkiness).

Effects of personalized versus fixed tactile cueing during daily life will also be explored via cortical, gait and turning outcomes in Table 1 during week 2 of cueing feasibility at home versus week 1. Daily life gait and turning metrics are exploratory.

Analyses will be performed on an intention to treat basis. However, for the home monitoring, we will exclude participants who will not use the sensors for at least 5 hours per day and 5 days per week. For the cueing intervention, we will exclude participants if they walk with cueing for less than 20 minutes per day or less than 5 days per week.

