### 3.5. Statistical methods

#### 3.5.1. Power analysis.

We computed power to detect differences in a larger reduction of PFC activity during personalized, compared to fixed, tactile cueing. Furthermore, we predict that personalized cueing will show less activation of PFC versus fixed cueing (i.e., more automatic). We conservatively assume 54 subjects, 27 for each group (personalized and fixed training), will be included in this analysis, based on recruitment of 60, and allowing for modest dropout (> 10%). We computed power for a repeated-measures ANOVA model with 1 between and 1 within subject effect based on the Geisser-Greenhouse F-test (equivalent to a mixed model). Using patterns of HbO2 levels comparable to previously published results(ref Stuart and Mancini JNPT), assuming between-subject variance of 0.08, modest intra-subject correlation of 0.2, and level of significance at 0.05, we find that power is 82% for the test of between-subject effects (cueing group comparison), and 94% for the test of interaction (differential impact of dual-task versus single-task walking between the personalized- and fixed-cueing groups).

We also computed sample sizes required to achieve at least 80% power for detecting group differences of at least 0.50 SD for measures of walking and turning in daily life with ANCOVA models, conservatively assuming covariate R2 equal to 20%. We set level of significance to 0.02, which is the average alpha level when employing the Holm correction method over 6 outcomes (see below). Under these assumptions, 36 patients (18 per arm) are required to achieve 81.2% power. Thus, our plan to recruit 30 per arm will result in adequately-powered tests while allowing for missing/insufficient data or patient dropout. One of the goals of this trial is to generate preliminary estimates of sensitivity of daily life gait and turning quality due to a cueing intervention. These estimates ultimately will be used to inform power and sample size computations for a larger clinical trial. The small intervention proposed here (30 per group) is not designed to be a highly powered trial itself, but will make use of a randomized, two-group intervention design. All computations were conducted using PASS v15 (PASS 15 Power Analysis and Sample Size Software (2017), NCSS, LLC).

We are not planning interim analysis, and we are not expecting to stop the recruitment early.

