## 4. Discussion

This project aims to characterize the cortical correlates of gait automaticity in PD, evaluate the effects of personalized, versus fixed, tactile cueing on automaticity and explore the feasibility and efficacy of using tactile cueing to improve gait and turning in daily life. The technologies used pose minimal risk and findings could inform more effective, individualized rehabilitation strategies to reduce falls and enhance mobility.

If we find a decrease in PFC activity and an increase in sensory activity only with personalized, closed-loop cueing, and not fixed, open-loop cueing, compared to baseline, this will support our hypothesis that personalized, closed-loop feedback improves gait automaticity. However, we expect to find improvements in walking and turning, measured in the laboratory (reduced stride-time variability, increased gait speed, reduced turning duration and turning jerkiness) with both cueing interventions. We will investigate which cueing modality is superior in improving gait and turning during daily life, when less attention is on gait [75]. If we find a a small effect size, then a greater sample size will be needed for a future, randomized, placebo-controlled clinical trial to improve daily mobility in people with PD.

This trial incorporates several innovative elements. It is among the first to combine portable fNIRS with wearable inertial sensors to assess both cortical activity and gait and turning measures in the laboratory, as well as investigating feasibility of using cueing and measuring effects on gait and turning in the real-world. The use of personalized, closed-loop tactile cueing, which delivers stimulation in real time based on the individual’s gait cycle, represents a major advancement over conventional fixed (open-loop) cueing systems. Unlike auditory or visual cues, the tactile modality targets proprioceptive pathways and may better engage subcortical circuits involved in gait automaticity [38,40].

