Another aspect of innovation is the fact that our cueing system is standalone, app-free design, allowing users to benefit from tactile cueing without relying on smartphones or external devices. The tactile stimulus occurs on simple bracelets on the wrists, which are easy to don and provides perceptible vibration to people with PD, who usually cannot detect vibration on the feet [76]. The cueing system has a simple switch to turn the stimulation on or off. This simplicity is especially important for people with Parkinson’s disease, who may experience cognitive or motor challenges that make app navigation difficult. By eliminating the need for digital interfaces, the system may enhance usability, accessibility, and real-world adherence, making it a practical solution for unsupervised use in daily life. The device’s personalized, closed-loop algorithm still operates in real time based on the user’s gait, delivering tailored cues, while maintaining a user-friendly, low-tech interface, which is a novel feature in the field of gait rehabilitation.

Furthermore, using instrumented socks allows for unobtrusive and continuous monitoring of gait in daily life, providing a rich dataset to evaluate how cueing affects mobility outside the laboratory. Likewise, the sensor on the elastic belt around the waist provides accurate measures of turning quality in daily life. By bridging neural, behavioral, and ecological data, this study can help next-generation, personalized rehabilitation strategies in PD and as well as other groups with gait impairments. Gait automaticity, or the ability to multitask while walking, is a critical, functional skill that may be improved with the addition of appropriate rehabilitation, such as cueing.

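### In the dual-task conditions a fall in PFC activity is read as better automaticity, yet AX-CPT performance is neither an outcome nor a model term, so reduced effort on the cognitive task cannot be ruled out

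*Protocol article*

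**What the plan says.** Section 3.4.1 sets four tasks: walking and 360-degree turning, each with and without a concurrent cognitive task. "The secondary cognitive task used in both dual-task conditions is a modified version of the Continuous Performance Test", described there as a test of attention and vigilance. All four tasks are done "first without cueing and then with cueing activated", in both arms.

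The reading of PFC activity is given in three places:

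- Background: "whereas if cueing improves automaticity, we will see decreased PFC activity".
- Objectives: "We hypothesize that personalized tactile cueing will reduce PFC activity (improve automaticity".
- Discussion: "If we find a decrease in PFC activity and an increase in sensory activity only with personalized, closed-loop cueing", and not with fixed cueing, compared with baseline, the hypothesis is taken as supported.

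On outcomes, section 3.4 (Outcome measures) states: "Primary and secondary outcome measures are summarized in Table 1, which includes the domains and metrics". Table 1 has three columns: cortical activity, gait and turning. The mixed model in section 3.5.2 (Statistical analysis) contains group, time point and their interaction, with Hoehn and Yahr, FOG and cognitive status as covariates. The power analysis in section 3.5.1 includes a dual-task contrast, claiming "94% for the test of interaction (differential impact of dual-task versus single-task walking" between the two arms.

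**The concern.** Under dual-task, PFC activity reflects demand from both gait and the AX-CPT. If PFC HbO2 falls when cueing is switched on, gait may need less executive control, or the participant may be putting less into the AX-CPT. The plan's reading allows only the first explanation, and nothing named as an outcome or covariate separates the two.

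This matters because the protocol itself says "Gait automaticity, or the ability to multitask while walking, is a critical, functional skill". On that meaning, performance of the second task is part of the construct. The Background already accepts the same kind of ambiguity for gait variability, noting that higher variability need not mean lost automaticity, but applies no matching caution to PFC activity under dual-task. The Objectives also expect fixed cueing to demand more attention to the cues, so the arms could plausibly differ in the attention left for the AX-CPT.

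**Working it through.** **Where AX-CPT performance could enter the plan**

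- Table 1: cortical, gait and turning measures only.
- Section 3.4 (Outcome measures): outcomes are chosen for their relation to automaticity (PFC activity, gait variability) or response to cueing (stride time, LDS, turn duration, turn jerkiness). No cognitive-task measure is named.
- Section 3.5.2: no AX-CPT term.
- Section 3.4.2: simple and choice reaction time, Trail-making, CLOX, digit span and line orientation are separate assessments. They do not show whether the AX-CPT was being done during the walk or turn.
- Discussion: the decision rule adds a sensory-cortex increase but no condition on the cognitive task.

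The article does not say whether AX-CPT responses are recorded. What it supports is that they are not used.

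**What disengagement does to each comparison**

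Suppose cueing has no true effect on PFC activity. Let a fraction f_P (personalized) or f_F (fixed) disengage from the AX-CPT in the cued block, each with a PFC drop of D.

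- Within-arm dual-task change from baseline: −f_P × D, or −f_F × D.
- Between-arm difference in change: −(f_P − f_F) × D.

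If f_P = f_F, the second expression is zero and the randomized contrast is unbiased, but both within-arm changes still show a fall. If f_P > f_F the bias favours personalized cueing; if f_F > f_P it works against it. In single-task conditions there is no second task, so D = 0.

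**Size**

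The documents give neither f nor D, nor the HbO2 means behind the power figures, so the stated 94% cannot be reproduced and the bias cannot be sized.

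Purely as an illustration, a yardstick can be back-solved. Inputs from section 3.5.1: 27 per arm, variance 0.08 (taken as total), correlation 0.2, alpha 0.05.

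- Variance of a within-person difference: 2 × 0.08 × (1 − 0.2) = 0.128.
- Standard error of the between-arm difference in change: √(2 × 0.128 / 27) = 0.0974.
- Group-by-task effect that gives 94% power (noncentral F, 1 and 52 df): 0.349 HbO2 units.

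Set D to one or two times 0.349, let one arm have an excess disengaging fraction, and assume the same correlation between uncued and cued measurements:

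| Excess fraction | D = 0.349 | D = 0.698 |
|---|---|---|
| 10% | 6.4% | 10.8% |
| 20% | 10.8% | 29.0% |
| 30% | 18.4% | 55.9% |

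Entries are rejection rates of the group-by-assessment test against a nominal 5%. They are the same if 0.08 is only the between-subject component (total 0.08 / 0.2 = 0.40; yardstick 0.780). The 0.349 is a between-arm interaction effect borrowed as a scale, not a dual-task increment from the documents. The table shows only that the result depends on unknown inputs.

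**What an added AX-CPT outcome could detect**

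With 27 per arm, two-sided 0.05 and 80% power, the detectable between-arm difference is 0.777 SD (noncentral t, 52 df). The 95% interval half-width is 2.007 × √(2/27) = 0.546 SD.

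**The case against.** The strongest reply is that this is an omission from a condensed article: scoring and engagement checks for a concurrent task may sit in a full protocol or analysis plan not shown here. That holds for scoring detail, and it is why nothing can be said about whether responses are collected. It does not dispose of the point, because the article does fix the outcome table and the rule for reading PFC activity, and neither refers to the second task.

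Other objections stand and limit the point:

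- A reader might infer that the reading of the primary outcome fails altogether. It does not. The PFC rule is stated for walking in general, and single-task walking and turning have no second task to abandon.
- A reader might infer that giving up the AX-CPT would by itself satisfy the trial's rule. The Discussion also requires a sensory-cortex increase with personalized cueing only, and the Objectives ask for accompanying gait and turning improvement. These are partial guards. Neither shows AX-CPT engagement, and gait could improve because attention has left the AX-CPT.
- A reader might infer that individual participants would be classed as improved. The analysis compares group means and has no responder definition.
- A reader might infer a bias towards personalized cueing. The only relevant statement, more attention to cues under fixed cueing, would lower PFC in the fixed arm if those participants dropped the AX-CPT, which works against the hypothesis. No passage says which arm would disengage more.

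**Conclusion.** The point holds for the two dual-task conditions. As written, the plan cannot separate more automatic gait from reduced effort on the AX-CPT there. The between-arm dual-task contrast is biased only if disengagement differs by arm, and then in either direction. The within-arm change from baseline is exposed even when disengagement is equal, because of the fixed uncued-then-cued order.

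The single-task results are untouched, and the overall conclusion is partly protected by the sensory-cortex and gait measures. No size can be attached from the documents; the rejection rates above rest on assumed inputs and should not be cited as the magnitude of a defect. The conclusion assumes only that effort on an attention task contributes to PFC activity, in line with the Background's account of the PFC as a cognitive control region. The change is worth making because it affects what the dual-task results can be said to show.

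**What to change.** If AX-CPT responses are recorded, list accuracy and response time as secondary outcomes, uncued and cued, for both walking and turning, and analyse them with the same group-by-assessment mixed model. Report the AX-CPT estimate and confidence interval beside every dual-task PFC result.

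Amend the interpretation so that a dual-task PFC decrease is described as improved automaticity only when read jointly with AX-CPT performance. Where performance falls, or the interval cannot exclude a material fall, report a possible task trade-off and rest the automaticity conclusion on the single-task conditions. What counts as a material fall should be set before unblinding. If responses are not recorded, the protocol should say so and limit the dual-task reading in the same way.

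The cost is wording in the outcome table and analysis section, one or two more secondary outcomes, and a more cautious dual-task conclusion. With 27 per arm the interval will often be too wide to rule out a moderate fall, so the joint reading should rest on the estimate and interval and not on a non-significant test.
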